### Intervention Details

The intervention comprises (1) the universal school lunch program and (2) the associated curriculum. The intervention will last 2 full school years (plus a summer between) to allow time for the schools to adapt to new food and curricular practices. Case study research will be ongoing over 20 months of school.

The school lunch will be offered every day at no cost to all students in the intervention schools and will focus on nutritious foods, including a variety of vegetables and fruits, whole grains, dairy products, plant proteins, and some meat. With SPSD staff and CHSF input, we developed a 6-week menu for the school food program with considerations for cultural appropriateness and the new CFG recommendations, including more plant-based proteins and whole grains. We are working with a community-based organization that works with local producers to incorporate local foods where possible into school food menus. The menu includes a variety of vegetables and fruits because they are particularly low in the diets of Canadian children [14,46], and it has been reviewed by a dietitian.

For curriculum integration, we adapted 6 lesson plans each from kindergarten up to grade 6 (ages 5-12 years) to teach food safety, food preparation, nutrition, gardening, and food waste reduction tied to the Saskatchewan curriculum and informed by our scoping review. The curriculum was developed with the CHSF and several Saskatchewan teachers and is ready to use in the classroom with little additional preparation by teachers. In addition to the lesson plans, all classrooms in each grade will also have two experiences involved in cooking: one indoor and one outdoor food-growing experience. Consistent with best education practices, our focus is on a hands-on curriculum.

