#### Phase 2 and Phase 4: Baseline and End Point Measurement

RQ2: What is the difference in diet quality, food group, and key nutrient consumption among children in intervention schools after the implementation of a comprehensive, curriculum-integrated universal school lunch program as compared with children in control schools?

A digital photography–enhanced plate-waste study will assess food eaten for lunch by students in intervention and control schools (n=148 minimum each for a total of 296; 4 schools) on 2 days at baseline (preintervention) and then on 2 days at the end point (in the last 2 months of the intervention). Each participating child will have four measurements of plate-waste data (two baseline and two end point data). We will follow the protocol developed by coinvestigator HV, which has been extensively used in studies of school-aged children [85-87]. The procedures for data collection involve weighing the served food and leftovers, using digital photography and a food scale during the lunchtime with an app installed on tablets. This method is considered the most precise measurement of dietary intake compared with other dietary assessment methods that are typically used, such as food records [88,89]. The literature indicates no significant impact of the method on eating behaviors in children [88,89]. Digital photography of plate-waste will be conducted by 2 research assistants in half the school classrooms on each data collection day, for a total of 4 data collection days at both baseline and at end point in each school. The practice of collecting data from half the classrooms in a single school on each data collection day will ensure minimal disruption of regular school days.

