#### Further Quantitative Analyses

Analyses of plate-waste data and survey data will be conducted using the intention-to-treat principle [96]. To assess the effect of the intervention, we will use mixed-effect models using time of measurement (baseline or end point), group (intervention or control), and an interaction between time and group as fixed effects (base model). The neighborhood of residence (proxy for SES) will be used to determine whether SES influences the response to the intervention. To account for clustering related to repeated measures and because of sampling of students within classes and schools, variables representing participants and schools will be included as random effects in all models. Additional models will account for potentially confounding variables identified using directed acyclic graphs for each outcome [97,98]. Directed acyclic graphs are used to identify potential confounders using prespecified conceptual diagrams and testing these using the data to increase the precision of estimates and causal paths based on regression models. Analyses will be conducted using the MIXED procedure in SAS version 9.4 (SAS Institute, Inc).

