## Discussion

### Principal Findings

In real-world settings, there are a number of potential challenges to this research, some we can anticipate now and some we will have to address as they come up. Fortunately, our team has a wealth of experience conducting research with children and school staff in the school environment. First, the research team is also an intervention team. As we are piloting a type of universal, curriculum-integrated intervention that is quite innovative, we do not think that operating separately would be either feasible or appropriate. Part of the strength of this research is the collaboration, and we will draw on this with the intention that future research, once the intervention has benefited from this intensive study, will be conducted separately from the intervention.

We have already encountered the challenge of the COVID-19 pandemic. This project was funded in April 2020; however, because of school closures between March and June 2020, and the uncertainty of opening schools during a pandemic, the project was delayed by a year. Baseline data were collected in May and June of 2021. The intervention will begin in September 2021 with the new school year, but as of July 2021, we do not know what new challenges will exist with case study data collection because of the pandemic. We will need to adapt our protocols to whatever public health measures are in place over the 2 intervention school years.

We may encounter challenges with curriculum integration with teachers and other school staff. To minimize this, we have developed an intervention and research with the school division and have already been collecting baseline data in the intervention schools on current practices and needs. We have practiced limited family and teacher engagement (due to the COVID-19 pandemic) within the schools and will adapt as needed to ensure that both families and teachers continue to participate.

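### Plate-waste models have no measurement-day term, although end-point diet in the intervention schools rests on at most 8 of about 30 shared menu days

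*Protocol article*

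**What the plan says.** Under Intervention Details, "The school lunch will be offered every day at no cost to all students in the intervention schools", and "we developed a 6-week menu for the school food program".

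Under Phase 2 and Phase 4: Baseline and End Point Measurement, plate waste is recorded "on 2 days at baseline (preintervention) and then on 2 days at the end point (in the last 2 months of the intervention". Research assistants work "in half the school classrooms on each data collection day", which gives each school "for a total of 4 data collection days at both baseline and at end point in each school". The half-school split is explained by the wish to disrupt the school day as little as possible. Recipe data for the collection days are entered in the app before lunch. The same section says that clustering within classroom and school will be handled by multilevel models, and that final models adjust for baseline intake.

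Under Further Quantitative Analyses, the base model has time, group and their interaction as fixed effects, and "variables representing participants and schools will be included as random effects in all models". Neither section names measurement day or menu as a model term.

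**The concern.** The design creates a dependence that the stated model leaves out. Before the intervention, lunches brought from home differ from child to child. At end point in the intervention schools, everyone in the measured half-school who takes the program lunch is served the same meal. Outcomes such as sodium, calcium, folate, vitamin D and food-group servings depend directly on what is served, so a menu that is unusual on one of them shifts all those children together.

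This shared shift arises mainly in one arm at one time point, so it falls inside the time-by-group contrast that measures the intervention effect. A participant or school intercept that is constant over time cancels from that contrast and cannot absorb it. At stake are the width of the interval and the error rate of the test, and also whether a few menus can stand for the six-week program.

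**Working it through.** **Reproducing the plan's count.** 2 days per child × 2 halves of a school = 4 days per school at each time point, as stated.

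**Coverage of the cycle.** 6 weeks × 5 school days = 30 menu days (the 30 is inferred, not printed).
- One child: 2/30 = 7%.
- One school: at most 4/30 = 13%.
- Both intervention schools: at most 8/30 = 27%.
- If four days were drawn at random, a given menu week would be missed with probability C(25,4)/C(30,4) = 0.46.
- A school's four-day mean would have a sampling SE of √[(1/4)(26/29)] = 0.47 between-day SDs around its cycle mean.

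**Effect on the test.** Inputs:
- n = 148 children per arm (Sample section), so 148/4 = 37 per school-day.
- Single-day variance is set to 1.
- Between-child share c = 0.3 (assumed).
- Menu-day share r = 0.01, 0.05 or 0.10 (assumed; the article gives no between-day variance).
- D = distinct menu days in the intervention arm: 8 if the schools use different days, 4 if they use the same ones.
- Finite-cycle factor f = (30 − D)/29.
- No day component in the control arm (assumed).

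Variance of an end-point arm mean if shared days are ignored:
V0 = c/n + (1 − c)/(2n) = 0.3/148 + 0.7/296 = 0.00439.

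Intervention arm with shared days:
V1 = c/n + (1 − c − r)/(2n) + f·r/D.

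For r = 0.05 and D = 8: V1 = 0.00203 + 0.00220 + (22/29)(0.05/8) = 0.00203 + 0.00220 + 0.00474 = 0.00896.

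The true variance of the arm difference relative to the assumed one is k = (V1 + V0)/(2·V0) = (0.00896 + 0.00439)/0.00878 = 1.52. The actual two-sided level is 2[1 − Φ(1.96/√k)] = 0.112.

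| Menu-day share r | k, 8 distinct days | Actual level | k, same 4 days in both schools | Actual level |
|---|---|---|---|---|
| 0.01 | 1.10 | 0.062 | 1.25 | 0.080 |
| 0.05 | 1.52 | 0.112 | 2.26 | 0.192 |
| 0.10 | 2.04 | 0.170 | 3.51 | 0.296 |

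**The same check on the change from baseline**, which is closer to the time-by-group contrast. Between-child variance cancels and baseline day-to-day noise is added:
- Days ignored: W0 = 0.7/148 = 0.00473.
- Intervention arm: W1 = 0.7/296 + (0.7 − r)/296 + f·r/D.
- For r = 0.05 and D = 8: W1 = 0.00236 + 0.00220 + 0.00474 = 0.00930, ratio (0.00930 + 0.00473)/0.00946 = 1.48, level 0.108.
- Over r = 0.01 to 0.10 the level is 0.061 to 0.162 with 8 days, and 0.078 to 0.283 with the same 4 days. The picture is unchanged.

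**More children do not help.** With all 340 eligible children per arm and 8 distinct days, the end-point calculation gives k = 1.24, 2.22 and 3.44, and levels of 0.079, 0.188 and 0.291. The term f·r/D does not shrink with n.

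**The case against.** The best counter-argument is that the planned models are not naive. Participants and schools are random effects in every model, and classroom clustering is mentioned as well. A reader might infer that the readings are analysed as independent; the text does not support that.

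Part of the menu-day variation could also reach the standard error. If a final model takes the end-point value as outcome and adjusts for baseline intake, a school's menu-day deviation falls into its end-point school effect, and half-school differences fall partly into the classroom effect. This stands, but only in part. Classrooms in the same half-school share the same menus, so their effects are not independent of each other. A school variance estimated from four schools is imprecise. If both intervention schools were measured on the same menus, the shared deviation could not be separated from the group effect. The base model with time-constant intercepts has no such partial protection.

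The article does not say how days are chosen within the last two months. That rule may sit in the plate-waste protocol that it cites, so its absence is not a fault here.

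A reader might also infer from "First, the research team is also an intervention team" that the program team picks favourable days and biases the effect upward. The article does not say who sets the dates, and nothing in it shows such bias.

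Finally, two weighed days per child, with half a school at a time, is a reasoned feasibility choice. It need not change.

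**Conclusion.** The point holds as a gap between the design and the stated model. The direction is clear: when menu-day variation is shared and not modelled, the standard error of the time-by-group effect is too small, and the result leans on at most 8 of about 30 menus.

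The size is not known. The range of about 0.06 to 0.17 for a nominal 0.05 test rests on an assumed menu-day share of 1% to 10%, an assumed between-child share of 0.3, 148 children per arm, eight distinct days and a five-day school week. It also takes the standard error to ignore day entirely, so a classroom effect or a baseline-adjusted end-point model would reduce the excess. Measuring both schools on the same menus would raise it, to about 0.08 to 0.30 under the same assumptions. The finding concerns precision and how well the cycle is represented; it does not establish bias in either direction. The change is worth making before end-point collection in May and June 2023.

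**What to change.** 1. Keep four end-point days per school and two per child. Spread them over different weeks and weekdays of the menu cycle, ideally by random draw, and use different menu days in the two intervention schools so that up to 8 of about 30 are covered.
2. Add a school-by-date random effect to the plate-waste models, with its variance allowed to differ for intervention schools at end point. A single common variance would average the 8 shared-menu school-days with the rest of the 32 school-days (4 schools × 4 days × 2 time points), most of which involve largely home-brought lunches, and would under-correct. At the least, prespecify this model as a sensitivity analysis.

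No extra staff or collection days are needed, and the recipe data for each day are already to be recorded. The cost is less flexible scheduling and a somewhat wider interval. With 8 school-days in the cell that matters, the day variance will itself be estimated imprecisely.

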#### Further Quantitative Analyses

Analyses of plate-waste data and survey data will be conducted using the intention-to-treat principle [96]. To assess the effect of the intervention, we will use mixed-effect models using time of measurement (baseline or end point), group (intervention or control), and an interaction between time and group as fixed effects (base model). The neighborhood of residence (proxy for SES) will be used to determine whether SES influences the response to the intervention. To account for clustering related to repeated measures and because of sampling of students within classes and schools, variables representing participants and schools will be included as random effects in all models. Additional models will account for potentially confounding variables identified using directed acyclic graphs for each outcome [97,98]. Directed acyclic graphs are used to identify potential confounders using prespecified conceptual diagrams and testing these using the data to increase the precision of estimates and causal paths based on regression models. Analyses will be conducted using the MIXED procedure in SAS version 9.4 (SAS Institute, Inc).

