### Sample

We conducted a sample size calculation that indicated that we needed a minimum sample of 148 children from 2 intervention schools matched with 148 children from 2 control schools to detect changes in eating behavior, accounting for attrition from the baseline (pretest) to the end point (posttest). Furthermore, 2 intervention and 2 control elementary schools were selected by the Saskatoon Public Schools Division (SPSD) from the 8 schools that currently have small lunch programs and the infrastructure to scale up to serve the whole school. Saskatoon is a midsized Canadian Prairie city with a population of approximately 325,000 residents. The 4 schools were selected from among the 8 schools because the school staff in these schools are willing to participate in this initial intervention study which is critical at this stage. The schools are located in lower SES neighborhoods with more ethnic diversity including relatively large numbers of newcomers and Indigenous children compared with other neighborhoods in Saskatoon [84].

Our sample of students in the intervention schools is a 1:1 matched sample of children from 2 control schools based on self-identified gender, age, school grade, and school neighborhood median income, who will be followed from the baseline to the end point (2 full school years with a summer break in between). All children in grades 1-6 in each school will be invited to participate (approximately 170 students in each school in these grades). Our total sample from which participants will be drawn is about 340 (170 in each school), much more than the minimum 148 needed in our sample size calculation. They will be matched with an equivalent number in control schools.

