The collated baseline and end point data will go through data cleaning, processing, and quality control using protocols developed in the [name] Nutritional Epidemiology laboratory. After creating the master data file including original and derived variables of interest, such as the Nutrient Rich Food index (9.3) [92], HEI [14] based on the new CFG, sex assigned at birth, self-identified gender, age, grade, and neighborhood of residence as a proxy for SES, the descriptive analyses will provide the initial information on these variables. Categorical variables (ie, HEI categories) will be summarized in frequency tables. Regression models will examine changes from baseline to the end point across key outcome variables including the Nutrient Rich Food index scores, HEI scores, CFG servings, and key nutrients (calcium, sodium, vitamin D, folate, and calories from minimally nutritious food) and whether changes differ between the control and intervention schools. Final models will adjust for potentially confounding factors including sex assigned at birth, self-identified gender, age, grade, neighborhood of residence, and baseline dietary intake (for more detail on identifying a priori potential confounders and controlling for them, see *Phase 5: Final Analysis and Dissemination* section below). We will also examine potential interaction effects between the intervention and control groups and age, sex, and gender (as detailed above in the sample description) to assess whether the effect of the intervention on dietary outcomes was modified by key student-level characteristics. Clustering of students within the classroom and schools (nonindependence) will be taken into account by applying random-effects multilevel modeling approaches to data.

RQ3: What is the difference in food-related KAP among child participants in intervention schools after the implementation of a comprehensive, curriculum-integrated universal school lunch program as compared with children in control schools?

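### With two plate-waste days per phase, a participant intercept alone makes the time-by-group standard error too small if the days enter as separate records and children differ in their change

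*Protocol article*

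**What the plan says.** In the protocol article, the section *Further Quantitative Analyses* describes one model for plate-waste and survey data alike. Its fixed effects are "time of measurement (baseline or end point), group (intervention or control), and an interaction between time and group as fixed effects (base model"). Its random part is that "variables representing participants and schools will be included as random effects in all models", and the declared purpose is "To account for clustering related to repeated measures and because of sampling of students within classes and schools". The software is SAS MIXED.

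The plate-waste design is in the section *Phase 2 and Phase 4: Baseline and End Point Measurement*: "Each participating child will have four measurements of plate-waste data (two baseline and two end point data"). The same section adds, for the dietary outcomes: "Clustering of students within the classroom and schools (nonindependence) will be taken into account by applying random-effects multilevel modeling approaches to data". That sentence concerns levels above the child.

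Neither section names a participant-by-time term, a day term, a within-phase covariance or an averaging step. Neither says that the participant effect is an intercept only.

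**The concern.** The survey yields one record per child per phase, and a participant intercept suits it. Plate waste has an extra level: days within a phase, and phases within a child. If all four days are entered with one participant intercept, two lunches from the same data-collection window must be exactly as correlated as two lunches two school years apart. The model then has no term for how an individual child's intake shifts between phases. Day-to-day differences within a phase, which say nothing about change, help to set the error against which change is tested.

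The article gives reasons to expect such shifts. Children are followed over two full school years. The article itself plans to "assess whether the effect of the intervention on dietary outcomes was modified by key student-level characteristics" and to ask whether neighbourhood SES influences response. At stake is the main test for every plate-waste outcome: HEI, Nutrient Rich Food index, food guide servings and key nutrients. The problem arises even with no school or classroom effect at all.

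**Working it through.** **Inputs from the article.** There are four plate-waste records per child, two per phase. The sample is "n=148 minimum each for a total of 296; 4 schools", so 148 children per group.

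**The plan's own figure.** The 148 cannot be reproduced, because alpha, power, effect size, SD and attrition rate are not given. For orientation only: with an assumed two-sided 5% level, 80% power and no attrition, 148 per group detects (1.960 + 0.842) × √(2/148) = 0.326 SD. Nothing below disputes the 148.

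**Assumed input.** Let r be the child-by-phase variance divided by the day-to-day variance. The documents give no value, so a range is shown. In terms of the same-phase correlation rw and the cross-phase correlation rb, r = (rw − rb)/(1 − rw).

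**Step 1: true variance of a child's change.** Set the day variance to 1. Each phase mean has variance r + 1/2 around the child's own level, so the change (end point mean minus baseline mean) has variance 2(r + 1/2) = 1 + 2r.

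**Step 2: variance under a participant intercept only.** Four records leave three within-child contrasts. Two are day differences within a phase, each with variance 1 when normalised. One is the change, with variance 1 + 2r. The model pools them: (1 + 1 + 1 + 2r)/3 = 1 + 2r/3.

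**Step 3: ratio and rejection rate.** True over model variance is (1 + 2r)/(1 + 2r/3), which equals 3(1 + rw − 2rb)/(3 − rw − 2rb). The actual level of a nominal two-sided 5% test is 2[1 − Φ(1.96/√ratio)].

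| r | Variance ratio | True SE / model SE | Actual level (formula) | Simulated, participant intercept | Simulated, phase means |
|---|---|---|---|---|---|
| 0 | 1.000 | 1.00 | 5.0% | 4.3% | 4.2% |
| 0.1 | 1.125 | 1.06 | 6.5% | 6.5% | 5.1% |
| 0.25 | 1.286 | 1.13 | 8.4% | 8.8% | 5.4% |
| 0.5 | 1.500 | 1.22 | 11.0% | 10.6% | 4.9% |
| 1 | 1.800 | 1.34 | 14.4% | 14.5% | 5.3% |

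The simulations used 148 children per group, 4,000 runs per row, complete data and no school, class or treatment effect. As r grows without limit the ratio tends to 3 and the level to 25.8%.

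**Worked row, r = 0.5** (for example rw = 0.5, rb = 0.25). The true SE of the time-by-group effect is √(2 × 2/148) = 0.164 day SDs. The model SE is √(1.333 × 2/148) = 0.134. REML fits with a participant intercept to 150 simulated data sets gave a mean SE of 0.134. Their rejection rate was 16.7%, but 150 runs are too few to estimate that rate well. A separate set of 300 REML fits at the same setting rejected 11.0%.

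**What the child-level repair leaves.** Suppose a school-by-phase variance of 0.01 day variances, also assumed. With two schools per arm it adds 2 × (2 × 0.01)/2 = 0.02 to the variance of the effect. At r = 0 the child-level variance is 2/148 = 0.0135, so the true variance is 0.0335 and a model without a school-by-time term rejects about 21% of the time. At r = 0.5 the figure is about 14%.

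**The case against.** The strongest reply is that the article does not state the model criticised here. The defect needs day-level records, a participant effect that is an intercept only, and r above zero. Time has two levels with no day term, one description serves both plate waste and survey, and baseline dietary intake is listed as an adjustment covariate, which suggests that the two baseline days are combined somewhere. If phase means are analysed, the problem vanishes. A condensed article may also leave such detail to an analysis plan that is not shown.

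This makes the point conditional but does not remove it. Averaging is stated nowhere. Nor is the article silent: it names the child-level random effect, says that it is there for repeated measures, and applies it to all models. An analyst who follows that text literally gets the standard error described above.

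Two tempting extensions fail:

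- A reader might infer that the planned age, sex and gender modification tests are inflated to the same degree. The article does not say that these are fitted as interactions with time by group. If end point intake is modelled with adjustment for baseline, a participant intercept handles the two same-phase days properly.
- A reader might take the shared programme lunch at end point as proof that same-phase lunches are more alike. A common programme shifts the group mean, which the time-by-group term absorbs. Only differences between children in their response raise r.

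**Conclusion.** The concern holds in conditional form. If the four days enter as separate records with a participant intercept, the time-by-group test on plate-waste outcomes is anti-conservative whenever r exceeds zero. Some child-level variation in change over two school years is likely, but its size is unknown. For r from 0.1 to 1 the nominal 5% level becomes about 6.5% to 14%. It stays at 5% if r is zero, and at about 5% for any r if the days are averaged first, as far as child-level variance is concerned.

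The documents do not support saying flatly that the standard error is too small, or that the false-positive rate is a particular figure such as 11%. The first needs a reading that the article leaves open, and the second needs correlations that it does not give. Nor does the repair make the main test valid by itself. With two schools per arm and no school-by-time term named, school-level change is a separate problem and may be the larger one. The survey outcomes, with one record per phase, are unaffected.

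**What to change.** State how the two days per phase enter the analysis. For the plate-waste outcomes, either:

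- keep day-level records and add a participant-by-time random effect in MIXED, alongside the participant effect; or
- analyse one mean per child per phase with the participant intercept.

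The two are equivalent only when both days are observed. If some children miss a day, the first option weights their phases properly. Use the same structure for any age, sex or gender modification test fitted as an interaction with time by group. Leave the survey model as it is.

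The cost is one extra random term or one averaging step, with no new data. Intervals widen by about 6% at r = 0.1, 13% at 0.25, 22% at 0.5 and 34% at 1, with a corresponding loss of apparent power. School-level change needs its own decision.

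### As stated, the random effects for participants and schools drop out of the time-by-group test, so it takes no account of schools changing differently over time

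*Protocol article*

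**What the plan says.** Under Further Quantitative Analyses, the effect of the intervention is to be assessed with mixed-effect models that have "time of measurement (baseline or end point), group (intervention or control), and an interaction between time and group as fixed effects (base model"). The random part is introduced with its purpose, "To account for clustering related to repeated measures and because of sampling of students within classes and schools", and then specified: "variables representing participants and schools will be included as random effects in all models". No school-by-time term and no classroom term is named. The section covers both the plate-waste and the survey data and names the SAS MIXED procedure, without a degrees-of-freedom method.

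The section Phase 2 and Phase 4: Baseline and End Point Measurement describes the dietary analysis separately. It says: "Clustering of students within the classroom and schools (nonindependence) will be taken into account by applying random-effects multilevel modeling approaches to data". Its final models also adjust for a list of covariates ending in "neighborhood of residence, and baseline dietary intake". For the survey, the same section speaks of comparing the two groups at end point.

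On the data, the Sample section gives a "minimum sample of 148 children from 2 intervention schools matched with 148 children from 2 control schools". The measurement section adds: "Each participating child will have four measurements of plate-waste data (two baseline and two end point data").

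**The concern.** A time-by-group interaction compares the change in one group with the change in the other. Anything that adds the same amount to a child's or a school's baseline and end-point values disappears from each change. A participant effect and a school effect that do not vary with time are of exactly this kind. The clustering protection that the section claims therefore does not reach the test it is meant to protect.

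What would matter for that test is schools moving by different amounts over the two school years for reasons unrelated to the programme. Several features of the study make some such movement plausible:
- the school division chose the four schools from those whose staff were willing;
- public health measures were expected to change during follow-up;
- half of a school's classrooms are measured on the same collection day, so day and menu effects are shared.

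If such movement exists, confidence intervals are too narrow, and ordinary differences between schools can be reported as a significant programme effect.

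**Working it through.** **Inputs from the article.** 148 children in 2 schools per group, so 74 per school if split equally (assumption). Two plate-waste records per child per wave. Four schools in all.

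**Inputs assumed.** Two-sided 5% test. Let ρ be the school-by-time ICC of child-by-wave means, that is, the share of the variance of a child's mean in one wave (child and school levels that stay constant over time left out) that all children of that school share in that wave. The article gives no ICC, so ρ is varied.

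**The plan's own figure.** The 148 per group cannot be reproduced, because the article prints no effect size, SD, power or attrition rate. Solving backwards for an individual-level comparison at 80% power, without clustering or attrition: d = (1.960 + 0.842) × √(2/148) = 0.326.

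**Step 1: does the school effect cancel?** A mixed model with time, group, time-by-group and random effects for school and child was fitted by REML to one simulated data set (4 schools × 74 children × 2 waves × 2 days; child variance 0.30, residual 0.65). Only the school variance was altered.

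| School variance | Time-by-group estimate | Its SE | SE of group main effect |
|---|---|---|---|
| 0 | 0.1025 | 0.0902 | 0.090 |
| 0.05 | 0.1025 | 0.0902 | 0.100 |
| 1.0 | 0.1025 | 0.0902 | 0.214 |

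The school effect widens the group main effect and leaves the interaction untouched.

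**Step 2: size for plate waste.** If schools share a wave-specific shift, the true variance of the interaction estimate exceeds the modelled one by about D = 1 + (74 − 1)ρ. The real type I error is 2[1 − Φ(1.96/√D)].

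| ρ | D | Type I error, formula | Simulated (4,000 trials) |
|---|---|---|---|
| 0 | 1.00 | 5.0% | 4.5% |
| 0.001 | 1.07 | 5.8% | not run |
| 0.01 | 1.73 | 13.6% | 14.2% |
| 0.02 | 2.46 | 21.1% | 21.2% |
| 0.05 | 4.65 | 36.3% | 36.9% |

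In the same simulations, a t test on the four school mean changes (2 df, critical value 4.30) rejected in 4.4% to 4.9% of trials.

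**Step 3: the survey.** Only grades 4-6 answer it. Taking half the children, 37 per school (assumption), D = 1 + 36ρ, which is 1.36, 1.72 and 2.80 at ρ = 0.01, 0.02 and 0.05. The type I error is 9.3%, 13.5% and 24.2%.

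**Step 4: classroom and child.** With 6 classes of about 12 per school (assumption) and class-by-time correlation only, D = 1 + (74/6 − 1)ρ. The type I error is 6.3%, 7.7% and 11.7% at 0.01, 0.02 and 0.05. A child-by-time variance of 0.10 (of a total of 1) with no school-by-time variation gave 7.8% in simulation.

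**Step 5: degrees of freedom and power.** With complete plate-waste data there are 296 × 4 = 1,184 records. Children, time and time-by-group use 296 + 2 = 298, leaving 886 residual df. Four schools in two groups supply 4 − 2 = 2. On 2 df, power at d = 0.326 is about 35%, 24%, 19% and 12.5% at ρ = 0, 0.01, 0.02 and 0.05.

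**The case against.** The strongest reply is that the article never uses the word intercept. It says random effects, and a fuller analysis plan could let the school effect vary over time and choose a small-sample df method. The 886 residual df apply only if residual df are used. This stands as a caution. But the section does name the random effects for all models, and a variable representing schools, entered as a random effect, is most naturally a time-constant one. If more is intended, the text has to say so.

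Three stronger readings are tempting and are not supported.
- A reader might infer that the false-positive rate is certainly far above 5%. The article gives no ICC. Near zero the inflation is trivial; it is more than double the nominal level at 0.01 and above.
- A reader might infer that classroom clustering is to be ignored. The measurement section promises to handle it, and the later section cites classes as a reason for its random effects. This is an inconsistency between two sections, not a declared omission.
- A reader might infer that every diet and survey result is affected. If the baseline-adjusted dietary model is fitted to end-point or change scores, or the survey is compared at end point only, a school random effect does enter the error of the group effect.

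It is also fair to say that low power on 2 df comes from a design with two schools against two, and is not an error of the model. That is true, but it does not justify error bars that hide it.

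**Conclusion.** The point holds for the time-by-group model. With only participants and schools as time-constant random effects, the standard error of the key contrast is the same whatever the school variance, so school-level change is left out of the error. For plate waste, the false-positive rate runs from about 5% at a school-by-time ICC of 0 to about 36% at 0.05, and is about 14% at 0.01. For the survey it is lower, about 9% at 0.01 and 24% at 0.05 on the assumed 37 children per school. These figures rest on an equal split across schools, complete records and a two-sided 5% test. The ICC values are illustrative. This is a stated analysis that can give wrong error bars, not a detail left for later, and it should be corrected before the end-point analysis.

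**What to change.** In Further Quantitative Analyses:
- Add a school-by-time random effect and a classroom effect, defined as the class attended in that wave. This also reconciles the section with the classroom promise in the measurement section.
- Add a child-by-time effect for the plate-waste data only. The survey is given once per wave, so there it cannot be separated from residual error.
- Test time-by-group on the school-level df (2). Equivalently, compare the four covariate-adjusted school mean changes with a 2-df t interval.
- Report the four school changes beside the pooled estimate.
- If the baseline-adjusted dietary model or the end-point survey comparison is used instead, keep the school random effect and apply the same small-sample df.

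The change needs analysis wording only and uses data already planned. Its price is a much wider interval: the critical value alone rises from 1.96 to 4.30. Power is low, about 24% at an ICC of 0.01 for the back-solved effect. That reflects having four schools, and the write-up should say so.
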